## LIST OF ABBREVIATIONS

ACTIBATE: Activating Brown Adipose Tissue through Exercise  
BAIBA:  $\beta$ -aminoisobutyric acid  
BAT: Brown adipose tissue  
BMI: Body mass index  
BRITE: Brown-in-white  
CAMD: *Centro Andaluz de Medicina del Deporte*  
CIT: Cold-induced thermogenesis  
DXA: Dual Energy X-ray Absorptiometry  
 $^{18}\text{F}$ -FDG:  $^{18}\text{F}$ -fluorodeoxyglucose ( $^{18}\text{F}$ -FDG)  
HRres: Heart rate reserve  
iMUDS: *Instituto Mixto Deporte y Salud*  
MIT: Meal-induced thermogenesis  
PET/CT: Positron emission tomography/computed tomography  
RCT: Randomized controlled trial  
REE: Resting energy expenditure  
RM: Repetition maximum  
SNS: Sympathetic nervous system  
UCP-1: Uncoupling protein 1  
VAS: Visual analogue scales

## COMPETING INTEREST

The authors declare that they have no competing interests

## ACKNOWLEDGEMENTS

The study is supported by the Spanish Ministry of Economy and Competitiveness, Fondo de Investigación Sanitaria del Instituto de Salud Carlos III (PI13/01393), Fondos Estructurales de la Unión Europea (FEDER), by the Spanish Ministry of Science and Innovation (RYC-2010-05957, RYC-2011-09011), by the Spanish Ministry of Education (FPU 13/04365), by the Fundación Iberoamericana de Nutrición (FINUT), by the Redes temáticas de investigación cooperativa RETIC (Red SAMID RD12/0026/0015), and by Vegenat ®.

## ABSTRACT

**Aims:** The energy expenditure capacity of brown adipose tissue (BAT) makes it an attractive target as a therapy against obesity and type 2 diabetes. BAT activators namely catecholamines, natriuretic peptides and certain myokines, are secreted in response to exercise. ACTIBATE will determine the effect of exercise on BAT activity and mass measured by positron emission tomography/computed tomography (PET/CT, primary outcome) in young adults. ACTIBATE will also investigate the physiological consequences of activating BAT (secondary outcomes).

**Methods:** ACTIBATE will recruit 150 sedentary, healthy, young adults (50% women) aged 18-25 years. Eligible participants will be randomly assigned to a non-exercise group (n=50) or one of two exercise groups (n=50 each). Participants in the exercise groups will perform aerobic and strength training 3-4 days/week at a heart rate equivalent to 60% of heart rate reserve (HRres), and at 50% of 1 repetition maximum (RM) for the moderate-intensity group, and at 80% of HRres and 70%RM for the vigorous-intensity group. Laboratory measures completed at baseline and 6 months include BAT activity and mass, resting energy expenditure, meal and cold-induced thermogenesis, body temperature regulation and shivering threshold, body composition and cardiovascular disease risk factors. We will also obtain biopsies from abdominal subcutaneous white adipose tissue and skeletal muscle to analyse the expression of genes encoding proteins involved in the thermogenic machinery.

**Discussion:** ACTIBATE will allow quantification of the dose-response of different exercise intensities (i.e. no exercise, moderate-intensity and vigorous-intensity) BAT activity and mass in humans. Findings from ACTIBATE will have significant implications for our understanding of exercise and its protective effects against the development of type 2 diabetes, obesity and related metabolic diseases.

ClinicalTrials.gov ID: NCT02365129

**Key words:** Brown adipose tissue; energy metabolism; thermogenesis; body temperature regulation; obesity; type 2 diabetes.

## BACKGROUND

Both obesity and diabetes are serious health problems. Obesity is one of the major risk factors for cardiovascular disease, diabetes and several types of cancer. Other factors such as osteoarthritis, chronic pain, asthma, gallbladder disease and metabolic disorders are also present in obese individuals [1]. Data from the International Diabetes Federation [2] estimates that in 2035 a total of 592 million people will have diabetes. For society, both obesity and diabetes has also substantial direct and indirect costs that put a strain on healthcare and social resources [2]. Obesity is already responsible for 2-8% of health costs and 10-13% of deaths in different parts of the EU Region. In US, obesity overtook smoking as the leading contributor to the overall disease burden in 2010 [3]. Both unhealthy diets and physical inactivity are the main causes of the increasing levels of obesity and insulin resistance, which in turn lead to compensatory hyperinsulinaemia and ultimately type 2 diabetes. Although much research has been done, it is evident that our current knowledge is insufficient and new approaches have to be harnessed and exploited.

The ability to oxidize glucose and lipids and to dissipate energy as heat makes brown adipose tissue (BAT) an attractive target for anti-obesity and type 2 diabetes [4]. BAT is highly regulated by the sympathetic nervous system (SNS) to increase body temperature when mammals are exposed to temperatures below thermoneutrality. The heat production is mediated by uncoupling protein 1 (UCP-1), an inner-membrane mitochondrial protein exclusively expressed in BAT [4].

In humans, it was for long believed that BAT was only present in newborns and was responsible for non-shivering thermogenesis [5, 6]. In 2009, a number of human studies showed that BAT exists and that is thermogenically active in adults [7-10]. More recently, brown adipocyte-like cells in white adipose tissue of both rodents and humans have been found. These cells, so called brown-in-white (BRITE, or beige) adipocytes, possess a multilocular morphology and express the brown adipocyte-specific UCP-1 [11, 12].

A potential clinical implication of activating BAT relates to the stimulation of resting energy expenditure (REE), meal-induced thermogenesis (MIT) [13] and cold-induced thermogenesis (CIT) [14]. In humans, MIT seems to be higher in those possessing BAT, so that they convert a higher proportion of the calories in the meal directly to heat than do individuals without brown fat [15]. CIT has been strongly correlated with BAT, and it has been estimated that BAT increases total energy expenditure on 200-400 kcal/day when humans are under cold conditions [16]. In addition, it has been proposed that even if BAT activation would not produce enough energy expenditure to induce a negative energy balance, it could exert metabolic benefits on the prevention and treatment of type 2 diabetes and associated dyslipidaemia [17-19].

The SNS, through adrenergic signalling, is the classical regulator of BAT; however, recent findings have shown a pool of novel BAT activators that sidestep the need for stimulating the SNS, such as cardiac natriuretic peptides [20], irisin [21],  $\beta$ -aminoisobutyric acid (BAIBA) [22], interleukin-6 (IL-6) [23], and fibroblast growth factor 21 [24]. Of interest is that both SNS and non-SNS BAT activators are sensitive to exercise, which opens new horizons to study the potential effect of exercise-based therapeutic interventions [25, 26]. Several studies conducted in animal models have reported an increased BAT activity and browning after an exercise-based intervention [21, 27-30], yet there is still some controversy [31-35]. In humans, there seem to exist a positive association of exercise with BAT and browning activity [36-38].

The primary objective of the ACTIBATE randomized controlled trial (RCT) is to quantify the dose-effect of different exercise intensities (i.e. no exercise, moderate-intensity and vigorous-intensity), on BAT activity and mass (primary outcome), and on REE, MIT, CIT, body temperature regulation and shivering threshold, body composition and cardiovascular

disease risk factors in young adults. We will also obtain biopsies from abdominal subcutaneous white adipose tissue and skeletal muscle to analyse the expression of genes encoding proteins involved in the thermogenic machinery.

## METHODS

The present study is a RCT (ClinicalTrials.gov ID: NCT02365129). The Human Research Ethics Committee of both University of Granada (n° 924) and *Servicio Andaluz de Salud (Centro de Granada, CEI-Granada)* approved the study design, study protocols and informed consent procedure. All participants will have to provide a written informed consent. Participants will be randomly allocated to the usual care (control), moderate-intensity exercise or vigorous-intensity exercise groups, and will be followed for 6 months during the exercise interventions. All the baseline and follow-up examinations will be performed in the same setting [*Instituto Mixto Deporte y Salud (iMUDS)* at the University of Granada and *Hospital Universitario Virgen de las Nieves, Granada, Spain*] and by the same investigators. The study will be performed following the ethical guidelines of the Declaration of Helsinki, last modified in 2013.

### Participants and selection criteria

Participants will be students from the University of Granada (Granada, Spain). The University of Granada has  $\approx 65,000$  graduate students, of which  $\approx 40,000$  are 18-25 years. Eligible participants should be 18-25 years old and should have a body mass index (BMI) between 18.5 to 35 kg/m^2. The inclusion and exclusion criteria are listed in Table 1. We decided to implement the intervention on young adults with a wide range of BMI because overweight and obesity at this age is associated with an increased risk of cardiovascular disease among future middle-aged adults [39]. Moreover, BAT seems to be related to age and BMI [9, 40], being higher in younger and thinner people. Thus, people aged 18-25 years old are expected to present detectable BAT activity and mass [10, 41]. Further, persons of this age are legally able to sign themselves informed consent to participate in ACTIBATE, and no ethical issues are raised due to participant's age and type of measurements to be undertaken in the study. Risks will be minimized by ruling out contraindications to the testing and training protocols via a health history and a thorough physical examination prior to the testing sessions. If any medical problems arise during the project, participants will be referred for medical evaluation and, if necessary, dropped from the study. ACTIBATE has subscribed private liability insurance covering participants, investigator's responsibility as well as the responsibility of any person involved in the study, provided that there is proper adherence to the protocol.

Information period: participants will visit the iMUDS in two occasions. In the first visit, participants will receive a thorough explanation about the study aims, measurements to be undertaken, study requirements of the participants, and intervention types. What participants can expect from the study will be clarified, and any questions will be answered. Potential interested participants will therefore receive a short web-based questionnaire to obtain information about age, weight, height, physical activity, weight during the last 3 months, current medical history and medication use, smoking and alcohol habits, and residence. Individuals who remain eligible after the first screening and express willingness to participate in the study will be invited to a second orientation session. In the second visit, participants will receive detailed written information about the study. Eligible participants who wish to participate in further screening will be asked to sign the informed consent. Participants will then be scheduled for their first baseline measurement visit. Figure 1 illustrates the participant flow from recruitment to randomisation.

### Randomization and blinding

Eligible participants will be randomly assigned after completing the baseline measurements to either the control or exercise training groups. The randomization will be computer generated. Assessment staff will be blinded to participant randomisation assignment. Participants will be explicitly informed on the group to which they will be assigned as well as on the study hypotheses and will be reminded frequently not to disclose their randomisation assignments to assessment staff in the follow-up measurements. For practical and feasibility reasons, the study will be conducted in waves of maximum 15 persons.

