In a separate day, participants will fill in at home several web-based questionnaires regarding dietary habits, quality of life, sleeping habits, etc. Physical activity and sleep quality will be assessed through accelerometry during a week, and dietary intake will be measured by three 24h recalls.

**Primary outcome:** To quantify the effect of exercise intensities on BAT activity and mass, we will determine the maximal and mean standardized uptake values. We will do a PET/CT scan (Siemens Biograph 16 PET/CT, Siemens, Germany) to each participant at the cervical and supraclavicular level until mediastinum, after an individualized cooling protocol [60]. Participants will rest in a room at 18-19°C for an hour wearing a temperature controlled water circulation cooling vest (Polar Products Inc., Ohio, USA) at a temperature 3°C above the individually measured shivering threshold (see below). One hour later, we will raise 1°C the water temperature, and we will inject 74MBq (2 mCi) of F-fluorodeoxyglucose (F-FDG) tracer and will rest for another hour with the cooling chest vest at the same room temperature. If the participant reports shivering, the water temperature will increase 1°C until shivering stops. During all the process the skin temperature will be monitored, as well as the systolic and diastolic blood pressure. Two nuclear medicine physicians will independently interpret the images from the PET/CT. Additionally, immediately before the cold exposure (thermoneutral conditions) and after one hour of cold exposure (before the tracer injection) we will collect a blood sample to determine markers of energy metabolism such as glucose, insulin, and non-esterified fatty acids.

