### Secondary outcomes

To investigate the metabolic consequences of activating BAT we will measure:

- **REE.** It will be measured by indirect calorimetry (CCM express®, Medgraphics, Saint Paul, MN USA). REE will be calculated from O2 and CO2 volumes, as well as from urine excretion nitrogen values.
- **MIT.** It will be determined as the increase in energy expenditure above the REE divided by the energy content of a standardized meal (50% REE, T-Diet Vegenat).
- **CIT.** We will measure energy expenditure with indirect calorimetry during cold exposure of the aforementioned cooling protocol.
- All calorimetric measures will follow the accepted standard to assure the validity of the tests [61].

- **Shivering threshold.** To determine the shivering threshold, participants will wear a temperature controlled water circulation cooling vest (Polar Products Inc., Ohio, USA). The cooling vest covers the clavicular region of the participant, as well as the chest and abdominals. During the cooling protocol, participants will stay in a room at a temperature of 18-19 °C in a semi-supine position. The cooling starts at a water vest temperature of 21°C and water will be gradually decreased until shivering occurs [62]. We will determine shivering both visually and by asking the participants if they are experiencing shivering.
- **Body temperature regulation.** We will monitor skin temperature during (i) cooling protocols previous to the PET/TC; (ii) shivering threshold protocol; (iii) MIT test; and (iv) exercise test. Participants will wear a set of iButtons (DS 1922L, Thermochron, iButtons®; resolution: 0.0625°C, accuracy: 0.5°C; Maxim, Dallas, USA) covering the standard skin points following ISO 9886-2004 [63] defined locations to measure skin body temperature, proximal, distal and skin temperature [64]. Peripheral vasoconstriction will be estimated through the gradient of two iButtons (forearm and fingertip) [65]. Moreover, subjective cold perception will be assessed by VAS. We will also monitor supraclavicular skin temperature since it seems to have predictive value for BAT detection in adult humans [62].

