| 

-Age: 18-25 years.

-BMI: 18.5-35 kg/m^2.

-Not engaged in regular physical activity >20 min on >3 days/week.

-Not participating in a weight loss program.

-Stable weight over the last 3 months (body weight changes <3 kg).

-Normal electrocardiogram.

-Participants must be capable and willing to provide consent, understand exclusion criteria and accept the randomized group assignment.

 | 

- History of cardiovascular disease.

- Diabetes or hypertension.

- Pregnancy, or planning to get pregnant during the study period.

-Medication for hypertension, hyperlipidemia, hyperuricemia or other illness.

-Beta blockers or benzodiazepines use.

-Smoking.

-Frequent exposure to cold temperatures (Granada is surrounded by high mountains where people can ski or do trekking).

-Taking medication for thyroid.

-Other significant medical conditions that are life-threatening or that can interfere with or be aggravated by exercise.

- Unwillingness to either complete the study requirements or to be randomized into control or training group.

- A first-degree relative with history of cancer.

 |

**Table 2.** Summary of time point measurements of the primary and secondary outcomes of the study.

| Measurements                   | 1-
Baseline
(week 0) | 2-
Week
4 | 3-
Week
8 | 4-
Week
12 | 5-
Week
16 | 6-
Week
20 | 7-
Post-int
(week 25) |
|--------------------------------|----------------------------|-----------------|-----------------|------------------|------------------|------------------|-----------------------------|
| Primary outcome         |                            |                 |                 |                  |                  |                  |                             |
| BAT activity and mass          | x                          |                 |                 |                  |                  |                  | x                           |
| Secondary outcomes      |                            |                 |                 |                  |                  |                  |                             |

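### Participants are told the study hypotheses although their own report of shivering helps set the cold stimulus of the week-25 primary scan

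*Protocol*

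**What the plan says.** Under Randomization and blinding, the protocol randomises late: "Eligible participants will be randomly assigned after completing the baseline measurements to either the control or exercise training groups". It then states: "Participants will be explicitly informed on the group to which they will be assigned as well as on the study hypotheses". Staff are masked: "Assessment staff will be blinded to participant randomisation assignment". At follow-up that masking relies on participants being reminded not to reveal their group.

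Under Secondary outcomes, the shivering threshold is found by cooling a water vest until shivering occurs: "We will determine shivering both visually and by asking the participants if they are experiencing shivering". No instrument for detecting shivering is named.

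Under Outcomes measures, the primary PET/CT follows individualised cooling. The vest runs 3°C above the individual's threshold for the first hour. It is raised by 1°C when the tracer is given and worn for a further hour. In addition: "If the participant reports shivering, the water temperature will increase 1°C until shivering stops". The read-out follows: "To quantify the effect of exercise intensities on BAT activity and mass, we will determine the maximal and mean standardized uptake values". Table 2 places both the shivering threshold and the brown fat measurement at baseline and week 25 only.

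**The concern.** In most imaging trials a participant's beliefs cannot reach an uptake value that masked physicians read from a scan. Here they can, because the scan is taken under a cold stimulus that depends partly on what the participant says. A participant who knows both the arm and the expected answer may report shivering sooner or later than otherwise. If that tendency differs between arms, the arms are scanned at different average water temperatures relative to their true thresholds, and part of the difference in uptake would reflect reporting rather than training.

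The shivering threshold is itself a secondary outcome, and the ratings of thermal sensation, thermal comfort and appetite are self-reported. The same expectation reaches those measures directly.

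**Working it through.** The protocol states no figure on this point, so there is none to reproduce. The check is whether each link from disclosure to primary outcome is in the text, and whether any safeguard breaks the chain.

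**The chain**

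1. *Knowledge.* Participants are told their group and the hypotheses (Randomization and blinding). No reason is given for the second disclosure.
2. *Threshold.* Shivering is judged by sight and by asking (Secondary outcomes). Self-report is one of two inputs.
3. *Vest temperature.* With threshold T, the water is at T + 3°C in the first hour and T + 4°C after tracer injection (Outcomes measures). An error in T passes one-for-one into the water temperature.
4. *In-session adjustment.* Beyond the scheduled 1°C rise, the only stated trigger for warming is the participant's report. Visual confirmation is not mentioned at this step.
5. *Outcome.* Standardized uptake values are read after this cooling.

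**The safeguards**

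| Safeguard | What it protects | Does it protect the cold stimulus? |
|---|---|---|
| Masked assessment staff | Handling and visual judgement | Partly, at the threshold test; not where staff act on the participant's report |
| Two independent image readers | Interpretation of the scan | No |
| Room held at 18-19°C | Ambient temperature | Not the water temperature |
| Skin temperature monitoring | Records the response | No stated rule uses it to set or verify the stimulus |

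**Timing.** Randomisation follows baseline, so no arm-specific expectation can act on the baseline threshold or scan. Differential reporting can act only at week 25. It would enter the time × group interaction, which is the planned test under Statistical analysis, and the baseline scan would not cancel it. This assumes that the week-25 scan uses the threshold remeasured at week 25, as Table 2 suggests. If the baseline threshold were reused, only step 4 would remain exposed.

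**Scale**

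- One in-session report, or a threshold placed 1°C away from its true value, moves the water by 1°C. Relative to the offset this is 1/3 = 33% or 1/4 = 25%. It describes the offset only and says nothing about uptake.
- Planned effects (Sample size): 10% × 50 g = 5 g (moderate) and 20% × 50 g = 10 g (vigorous).
- The protocol gives no relation between water temperature and measured brown fat, so any bias in grams is an assumption. A between-arm bias of 1, 2.5 or 5 g would equal 20%, 50% or 100% of the 5 g effect, and 10%, 25% or 50% of the 10 g effect.
- Two-sided t-test with no true effect, n = 17 per group, df = 2 × 17 − 2 = 32, noncentrality = b / (SD × √(2/17)), where √(2/17) = 0.343:

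| Assumed bias b | SD 50 g (stated): noncentrality, rejection rate | SD 5 g (assumed): noncentrality, rejection rate |
|---|---|---|
| 1 g | 0.06, 5.0% | 0.58, 8.7% |
| 2.5 g | 0.15, 5.2% | 1.46, 29% |
| 5 g | 0.29, 5.9% | 2.92, 81% |

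The 5 g standard deviation is not in the protocol. It is roughly the value at which 17 per group would have 80% power for 5 g. The two columns show how far the consequence depends on inputs that the protocol does not settle.

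**The case against.** Several points on the other side have force.

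- *The disclosure adds little.* Participants already receive a full explanation of the aims before consent (Participants and selection criteria). The trial's name, spelled out, says that exercise activates brown fat. Knowing one's arm could alone produce the same behaviour. This stands: removing one clause leaves much of the expectation in place, so the information visits need neutral wording too.
- *The weak link is how shivering is ascertained.* This also stands in part, and it is why the remedy includes a scripted question. That question still relies on self-report.
- *Visual judgement limits the problem.* It does at the threshold test, if those watching for shivering belong to the masked assessment staff: a participant holding out against the cold may still be seen to shiver. The in-session rule mentions no such check.
- *The contrasts are not equally exposed.* Both exercise arms would expect a benefit, so moderate versus vigorous is less exposed than exercise versus control.

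Three stronger readings might be inferred, and the documents do not support them. First, that exercisers would endure more cold and so raise their uptake: nothing says that participants are told how water temperature affects the scan, or that arms would behave in opposite ways. Second, that the bias can be stated as a percentage of uptake: that needs both a change per degree and a mean temperature difference between arms, and the protocol gives neither. Third, that disclosure would prompt controls to start exercising: controls already receive advice and pamphlets on the benefits of activity, and activity monitors are worn by everyone at baseline and weeks 8, 16 and 25.

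**Conclusion.** The point holds as a risk of expectation bias in the primary outcome, confined to the week-25 threshold and scan and bearing mainly on exercise versus control. Every link is in the protocol, and neither staff masking nor dual image reading fully protects the cold stimulus. It is not evidence that the result will be biased, and neither direction nor size can be derived. The gram and error-rate figures above are illustrations under assumed biases. At the stated standard deviation of 50 g, even a 5 g bias barely moves the false-positive rate (5.0% to 5.9%), although it would equal the whole planned moderate-arm effect in the estimate.

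The conclusion assumes that the week-25 threshold is used for the week-25 scan and that participants' reports can be influenced by expectation. Since arm knowledge and part of the hypothesis reach participants anyway, this is an inexpensive improvement worth making rather than a flaw that undermines the design.

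**What to change.** 1. In Randomization and blinding, delete the clause on informing participants of the study hypotheses. Keep the statement that they are told their group.
2. At the information visits and at allocation, describe the aim neutrally: three programmes are compared, and their effect on brown fat is not known.
3. In the shivering threshold and PET/CT procedures, have blinded staff put the same scripted question about shivering to every participant at baseline and week 25.

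The cost is rewording the participant information and writing a short script. Participants hear slightly less about the expected direction, while purpose, procedures, risks and allocation remain fully explained. Sample size, visit schedule and equipment are unchanged. The change narrows the route for expectation bias and does not close it.
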